### 2.3. Participants

The study is conducted in the city of Erlangen, Germany. Adult outpatient participants with major depression are recruited. The patients are informed via flyers and posters at the hospital as well as via newspaper entries. Study email and phone numbers are provided where interested parties can ask questions and sign up for the study prescreening. A weblink for the prescreening is then sent out to test for eligibility criteria including Patient Health Questionnaire (PHQ-9) as a multipurpose instrument to assess depression severity. Interested persons who prefer a telephone pre-screening to the online link can also choose to do so. If eligible, potential participants are contacted and invited to an in-person meeting with a physician to receive explanations about the study content and procedures and are asked to sign the informed consent form. Participants continue to receive treatment as usual offered by their psychotherapist or medical doctor.

### 2.4. Eligibility Criteria

The inclusion criteria are patient ages between 18 and 75 years and major depressive disorder (Diagnostic and Statistical Manual of Mental Disorders (DSM)-5) [39], which includes recurrent, isolated, and bipolar forms. The exclusion criteria include patients with psychotic symptoms, acute suicidality, prior intolerance to body therapeutic methods, patients who are not able to attend the treatments for organizational reasons, patients who are not able to walk, speak, or clap their hands, and patients with a diagnosis of dementia, including vascular and neurodegenerative forms.

### 2.5. Sample Size

A sample size of 120 was calculated for the primary hypothesis: TaKeTiNa results in a significant pre-to-postintervention decrease in depression severity (combined IG1 and IG2 groups). According to the sample size calculation (one-tailed *t* test, difference between two dependent means, significance level 0.05, power 0.80, G*Power 3.1.9.7, downloaded 2020), 52 participants in the intervention group are sufficient to demonstrate a Cohen’s d of 0.35 and thus even a small effect size. Anticipating a dropout rate of 15% and striving for equal group sizes, our study aims to enroll a total of 120 participants who are evenly distributed between the intervention and control groups.

### 2.6. Randomization/Blinding

Participants are assigned a unique, sequential three-digit number code based on their screening order, with the assignment list securely destroyed after data collection. This proposed study is designed as a wait-list-controlled randomized group pilot study in which patients are randomly allocated to the IG and CG. This randomization process involves sorting participants by sex and age and then alternately assigning them to either the IG or CG to ensure nearly age-matched groups. Raters for rater based interviews are blinded.

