## Abstract

Background/Objectives: Depression is a prevalent and debilitating illness that significantly affects psychological and physical well-being. Apart from conventional therapies such as psychotherapy and medication, individuals with depression often lack opportunities for activities that are generally perceived as enjoyable, such as music, meditation, and arts, which have demonstrated therapeutic effectiveness. TaKeTiNa music therapy has been employed as a therapeutic intervention for more than two decades. However, there is a notable absence of well-designed clinical trials investigating its antidepressant effects, a gap we aim to address in our current study. Furthermore, shifts in the progression of depression may manifest both psychologically, by influencing emotional states, and physiologically, by leading to alterations in lipid and sphingolipid metabolism, cortisol levels, and immune system function. Our study seeks to analyze the impact of TaKeTiNa music therapy on both levels. Methods: This is a prospective monocentric randomized waitlist-controlled clinical trial. It investigates the influence of TaKeTiNa music therapy on patients with major depression in an outpatient setting. Therefore, interested persons are randomly assigned to two groups, an intervention group or a control group, after completing a screening procedure. The intervention group starts with an eight-week TaKeTiNa music therapy intervention. The waiting group receives the same therapy program after completing the follow-up period. Blood and saliva sampling as well as responses to questionnaires are obtained at specific time points. Discussion: Our study investigates the effects of TaKeTiNa music therapy, a non-pharmacological antidepressant treatment option, on depressive symptoms. We also address functional and causal immunological changes; hormonal changes, such as changes in cortisol levels; and metabolic changes, such as changes in serum lipids and sphingolipids, during the course of depression. We expect that this study will provide evidence to expand the range of treatment options available for depression.

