## 2. Materials and Methods

### 2.1. Study Design

This is a prospective monocentric randomized waitlist-controlled clinical trial investigating the influence of TaKeTiNa music therapy for patients with major depression in an outpatient group setting on the primary and secondary outcomes of depression.

Participants are randomized to either the intervention group (IG) or control group (CG). After the end of the follow-up period, the CG is offered the intervention. To reach the target numbers of participants, there are two consecutive rounds each of intervention (IG1 and IG2) and control (CG1 and CG2) groups. The combined IG1 and IG2 groups are defined as patients who start TaKeTiNa treatment. The combined CG1 and CG2 groups include patients who start with a waitlist (Figure 1).

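### Section 2.6 calls allocation random but describes a fixed rule, alternation down a list sorted by sex and age, which weakens the IG versus CG comparison and the randomised label

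*Protocol article*

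**What the plan says.** The Abstract states that "interested persons are randomly assigned to two groups, an intervention group or a control group, after completing a screening procedure". Section 2.1 opens with "This is a prospective monocentric randomized waitlist-controlled clinical trial" and adds that, to reach the target number, "there are two consecutive rounds each of intervention (IG1 and IG2) and control (CG1 and CG2) groups".

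Section 2.6 repeats that "patients are randomly allocated to the IG and CG". Its next sentence gives the mechanism, "This randomization process involves sorting participants by sex and age and then alternately assigning them to either the IG or CG", and the purpose, "to ensure nearly age-matched groups". The only safeguard stated there is "Raters for rater based interviews are blinded", which concerns outcome assessment and not the assignment of patients.

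Section 2.2 lists two leading hypotheses: a fall in depression severity from V1 to V3 within the combined IG, and a larger fall in the combined IG than in the combined CG. Section 2.5 bases the sample size on the first of these.

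**The concern.** The label and the mechanism do not agree. A reader of the Abstract or Section 2.1 would assume that chance decided who received therapy first. Under Section 2.6, a person's position on a sorted list decides it. This is not a detail left to a fuller document, because the article states the rule and the reason for it.

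The comparison with the waitlist is what would separate the therapy from spontaneous improvement and from the usual treatment that continues in both arms (Section 2.3). Participants in a waitlist design know their arm, so sound allocation is one of the few protections that this comparison has. If assignments can be foreseen or altered by someone who knows the patients, selection bias in the IG versus CG difference cannot be excluded.

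**Working it through.** **1. The plan's own figure.** Inputs from Section 2.5: one-sided paired t test, alpha 0.05, power 0.80, d = 0.35. The noncentral t distribution (n − 1 degrees of freedom, noncentrality 0.35·√n) gives n = 52 with power 0.801, as stated. The total follows as 52 × 1.15 = 59.8, so 60 per arm and 120 in all. The calculation uses IG data only. The allocation method does not enter it, and the fix leaves it unchanged.

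**2. How many allocations each scheme allows.** Inputs: 120 participants split 1:1 (Section 2.5) and two rounds (Section 2.1).

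| Scheme | Possible allocations |
|---|---|
| As written: sorted list, fixed starting arm | 1 |
| Random starting arm per round (not stated) | 2 × 2 = 4 |
| Random starting arm per sex list and round (not stated) | 2^4 = 16 |
| Random draw within 60 matched pairs | 2^60 ≈ 1.15 × 10^18 |

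As written, each person's probability of IG, given the list, is 0 or 1. With a random start it becomes 1/2, but knowing one person's arm reveals the arm of everyone else on that list.

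**3. What this means at the nominal level.** Section 2.9 sets alpha at 0.05. The smallest p-value that a randomisation test can reach is 1 divided by the number of equally likely allocations: 1/4 = 0.25 with a random start per round, or 1/16 = 0.0625 per sex list and round. Both exceed 0.05, and with a single allocation no such test exists. A t test can still be computed, but its validity then rests on modelling assumptions and not on the allocation.

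**4. Where the allocation could be altered.** Three openings follow from the text.
- The starting arm is not fixed by any stated rule.
- The order of people with the same sex and age is not defined.
- One person added or removed changes the arm of those who follow on the list. How many depends on whether alternation restarts for each sex, which Section 2.6 does not say.

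The third opening is practical. Section 2.4 excludes people who cannot attend for organisational reasons, which needs judgement. Table 1 marks the eligibility criteria at screening and again in the V1, V3, V4 column. The article does not say whether allocation comes before or after V1, or when a round's list closes.

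**5. Is age imbalance the problem?** It is not. With m people of one sex, ages uniform on 18 to 75 (range from Section 2.4; the distribution is an assumption) and the same arm always starting, the expected age gap is 57/(m + 1) for even m. For m = 30 this is 57/31 = 1.84 years. In 5,000 simulated trials with 30 per sex in each of two rounds, the mean gap was 1.84 years and the starting arm was younger every time. With about 35% of one sex and a varying split, the gap is about 0.9 years. The gap is systematic but small.

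**The case against.** **Arms are not certain at recruitment.** A list sorted by sex and age can exist only once a round is assembled, and the Abstract places assignment after screening. A reader might infer that recruiters know the arm of the next arrival, as in alternation by order of arrival. The documents do not support that: until the list closes, a candidate's position is open. This objection stands, and it places the risk with whoever controls the list.

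**Steering is not documented.** A reader might infer that patients were steered into therapy. The article does not say who sorts, who holds the list or how the starting arm is chosen, and nothing in it shows interference. It is also fair that a condensed article may leave out who generates and conceals a sequence. The point therefore cannot rest on silence about concealment. It rests on the stated rule, which is deterministic.

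**There may be an unreported random start.** The wording of Section 2.6 need not be exhaustive. A random start would leave 4 or 16 possible allocations, which does not cure the defect.

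**The powered hypothesis is untouched.** A reader might infer that the main test is invalid. It is a pre-post change within the IG and makes no use of the allocation. This limits the scope, but the IG versus CG hypothesis and the design label remain affected.

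**Conclusion.** The point holds in a bounded form. Section 2.6 claims random allocation and describes a systematic rule with no stated chance element or concealment. Given a round's list and starting arm, one allocation is possible, and it could be changed through the starting arm, the handling of ties, or a late change to the list.

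The consequence is that selection bias in the IG versus CG comparison cannot be excluded. Its size and direction cannot be estimated from the article, and no figure for it is offered. The word randomised in the Abstract and in Sections 2.1 and 2.6 is not supported by the method given. The pre-post hypothesis within the IG and the sample size of 52 evaluable (120 enrolled) are unaffected, and balance on age and sex is not the difficulty.

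The conclusion assumes that Section 2.6 describes the method actually used. If a full protocol specifies a random draw within matched pairs, Section 2.6 is misworded and only the text needs correcting.

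**What to change.** Rewrite the allocation paragraph in Section 2.6:

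1. Lock the round's participant list after eligibility is confirmed and V1 assessments are complete.
2. Sort by sex and age as now, with a written rule for ties.
3. Form consecutive pairs within sex. If both sex lists have an odd number, the two people left over form the last pair.
4. Let a computer-generated random draw decide which member of each pair goes to IG, with the seed and output kept on file.
5. Have this done once per round by existing staff who take no part in recruitment or rating.

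For any round already allocated by alternation, describe it as quasi-randomised in the Abstract and in Sections 2.1 and 2.6. Present its IG versus CG result without relying on randomisation for a causal claim.

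The cost is one paragraph and a few lines of code. No extra patients are needed, N does not change and the age and sex matching is kept. The one scheduling demand is that V1 must be finished for the whole round before the draw. The sort already requires the round to be assembled. For rounds already allocated, the remedy is limited to accurate labelling and more cautious inference.

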### 2.7. Intervention—TaKeTiNa Music Therapy

Participants follow an 8-week protocol with a total of 14 TaKeTiNa units (28 h total) under the supervision of a certified TaKeTiNa teacher. The intervention takes place in a sufficiently large group room at the university hospital. A group may contain a maximum of 35 persons based on previous experience of TaKeTiNa teachers with groups of around 50 individuals.

There is an introductory full day consisting of 3 units. Thereafter, a weekly TaKeTiNa unit is conducted. After 4 weeks, there is another full-day session consisting of 3 units followed by 4 more weekly units. For questions concerning individual participants, at least one medical doctor experienced in psychiatry is always available for the duration of the session. Since the sessions take place at the university hospital, staff in the emergency department of psychiatry are available in case of psychiatric decompensations for the duration of the session or afterwards.

The sessions are generally divided into five stages:Introduction: A brief explanation of the purpose of the session is provided. After that, the teacher introduces the topic (Supplementary Materials List S1) of the session that the participants should pay attention to and to refer to during the rhythmic process.Building the rhythmic foundation: The teacher chooses a TaKeTiNa rhythmic journey among the basic available journeys (Supplementary Materials List S2). Participants gather in a circle. The teacher leads the participants into a repetition of syllables, which facilitates orientation in the music cycle, with a bass drum instrument (Surdo, Remo, CA, USA) in the middle of the circle providing the main rhythm for the process. Then, specific repeating footsteps following the bass drum rhythm are introduced that the participants perform throughout. Last, single or multiple claps are added to introduce a second layer of rhythm that the participants perform. Once the participants are stable in terms of the repeating pattern of talking syllables, stepping, and clapping, the teacher begins the rhythmic journey using a percussive string instrument (Berimbau, Afroton Röttger, Frankfurt am Main, Germany).Rhythmic journey: As the group continues the rhythmic pattern with feet and claps, the teacher moves in the middle of the circle and starts a call response of different melodies and syllables, which the participants sing back as a whole group after they have finished one cycle. The Berimbau provides a subdivision of the main rhythm, making it easier to follow rhythmic melodies in, e.g., the offbeats. The purpose is to use stabilizing and destabilizing rhythms with the voice to increase the flexibility of the participants.Relaxation: As the music slowly fades, the participants are asked to increasingly go inward, with more gentle movements and voices until all movements and sounds subside into an inner feeling of the rhythmic patterns and the participants lay down for approximately 5 min.Integration: Participants and teachers gather in a circle sitting. There is an invitation to share experiences. Here, typical experiences, behavioral patterns, and emotions experienced can be shared and discussed.

### 2.8. Assessment (Primary and Secondary Endpoints)

#### 2.8.1. Data Collection

The data are documented through our study center and can be exported for analysis. Data collection and storage: The data are collected in pseudonymized form on paper and electronically. In all paper and online surveys, participants are encouraged not to provide any data allowing their identification but only their study patient number. The data concerning study findings are digitally stored on the server of the University Hospital Erlangen for 30 years in compliance with data protection regulations. Only the study leaders have access to the reference list (in paper form). The participants can withdraw their consent to participate in the study at any time without giving any reason until the reference list is destroyed after completing the study evaluations. Personal data (e.g., informed consent forms) as well as possible adverse events are stored in paper form in the university hospital in compliance with data protection regulations.

Depression severity and further psychometric scale scores are assessed at regular time intervals (Table 1). The 17-item Hamilton Rating Scale for Depression (HAMD-17) [40] is used to record the primary endpoint, i.e., rater-based depression severity. A trained rater (a physician or medical student assistant) conducts the HAMD-17 interview at the same time as the Montgomery–Åsberg Depression Rating Scale (MADRS) [41]. For further psychometric endpoints, we use the German versions of the Beck Depression Inventory II (BDI-II) [42] for self-evaluation, the Male Depression Rating Scale (MDRS-22) [43,44], and the Beck Anxiety Inventory (BAI) [45]. To additionally assess mindfulness, two scales are utilized: the Mindful Attention and Awareness Scale (MAAS) [46] and the German version of the Five Facet Mindfulness Questionnaire (FFMQ-D) [47,48]. We also determine the effects of the intervention on stress, sleep, and social anxiety by administering the Perceived Stress Scale (PSS-10) [49,50], the Resilience Scale (RS-25) [51], the Pittsburgh Sleep Quality Index (PSQI, [52]), and a German questionnaire for social anxiety and deficits in social competence (“Fragebogen zu sozialer Angst und sozialen Kompetenzdefiziten”, SASKO) [53]. To investigate how personality might influence the response to TaKeTiNa, patients are asked to complete the Big Five Inventory-10 (BFI-10, [54]), a 10-item scale measuring the Big Five personality traits, extraversion, agreeableness, conscientiousness, emotional stability, and openness. All self-evaluation questionnaires are completed online, pseudonymized, at home by the participants. The electronic system enables participants to pause the survey at any point and resume at a later time, allowing them to proceed at their own pace with breaks as needed.

#### 2.8.2. Blood Collection and Analysis and HRV

For biomarkers of the immune system, inflammation, hormones, and sphingolipid parameters, fasted blood samples are collected in serum and EDTA plasma vials at study inclusion, after the last therapy session (or after the two months of waiting), and again two months later (V1, V3, and V4) before 10 a.m. in the morning. Participants are asked to abstain from eating, drinkink, and consuming caffeine or nicotine in the morning prior to the study assessment. After centrifugation, the serum and plasma supernatants are stored as aliquots at −80 °C. A buffy coat from one EDTA vial is used to obtain leukocytes after erythrocyte lysis, which are stored as dry pellets for determination of cellular enzyme activities or stabilized with RNAlater for gene expression analysis via quantitative polymerase chain reaction. The blood samples will be analyzed by measuring the concentration of biomarkers such as growth and immune factors using commercial antibody-based and other detection methods. The activities of enzymes involved in sphingolipid metabolism will be determined via established assays using fluorescently labeled substrates [55,56]. Peripheral blood mononuclear cells are isolated by Ficoll gradient centrifugation and stored at −150 °C for subsequent immunophenotyping. Routine laboratory parameters are assessed at the Central Laboratory of the Universitätsklinikum Erlangen, Germany (DIN EN ISO 15189 accredited; available online under https://www.zentrallabor.uk-erlangen.de/ueber-uns/akkreditierung/ (accessed on 14 April 2024)) and at the Institute of Transfusion Medicine of the University Hospital Erlangen (D-ML-13297-01-00 accredited; available online under https://www.transfusionsmedizin.uk-erlangen.de/fileadmin/einrichtungen/transfusionsmedizin/dateien/2022-11_DAkkS_Urkundenanlage_D-ML13297-01-00.pdf (accessed on 14 April 2024), from separately collected vials. HRV is assessed with the “Elite HRV”^®^ app for mobile systems (ELITE HRV, Asheville, NC, USA) using a Polar H10 ECG® heart rate sensor with chest strap (Polar H10, Kempele, Finland) (Table 1).

### 2.9. Statistical Analysis

The statistical analysis will be conducted using latest version of the SPSS software available at the time of analysis. Group descriptions will be reported showing sociodemographic data as well as relevant primary and secondary outcomes. The nominal significance level will be set at α = 0.05.

### 2.10. Safety

For each participant, there will be three appointments for blood samples (approximately 30–40 mL of blood, i.e., approximately 100 mL in total in four months) and four time points to fill out the online questionnaires. Similar to mindfulness-based practices such as meditation, TaKeTiNa leads to increased awareness. In some cases, such practices can lead to a stronger experience of difficult feelings and thereby exacerbate psychological problems. If study subjects experience an increase in psychological symptoms, they can contact our emergency unit at any time and immediate psychiatric help will be offered. Therefore, we conclude that the potential benefits outweigh the potential risks. People who score more than four on PHQ-9 are asked to call our outpatient care unit for an appointment. If participants show suicidal thoughts in the screening interview (conducted by a medical doctor), treatment options will be discussed with the patients and clinical care will be offered. At least one medical doctor experienced in psychiatry is always available for the duration of the TaKeTiNa units.

Criteria for withdrawal from the study: Each participant has the possibility to withdraw the informed consent. We exclude patients who report suicidal tendencies, severe somatic illness, or admission to the hospital during participation.

